#### ML ensemble model—unsupervised ML

Time Series Split cross-validation (CV) will be used during model training and meta-learning stages. K-means and hierarchical clustering methods will be used for the clustering analyses. The clustering analyses will be performed within each CV fold. The optimal number of clusters for the clustering analyses will be determined using both the Calinski-Harabasz Index and Silhouette Scores.^16
36^ The final number of clusters will be selected based on the estimates from these two methods and applied.

The clustering analyses will be used to observe any differences in the clustering patterns across the outcomes.^16
37
38^ These methods can uncover patterns from the data structure without prior information or further input to the analysis.^39^ By interpreting the most decisive variables during the clustering process additionally using decision trees, their importance in predicting the outcome can be evaluated in the process. K-means clustering will be used to group unlabelled data into the pre-estimated number of distinctive clusters depending on their distances from each other.^38^ The algorithm iteratively runs until there are no significant changes to the clusters. Hierarchical clustering groups two observations together which are most similar, and is iteratively updated until the pre-estimated number of distinctive clusters is reached.^37^ Decision trees will be used to aid interpretation of the clustering decisions from both analyses to determine the important contributing variables to the outcome.^16^ If a difference in the clustering patterns over the outcome is observed, we can interpret the most determining variables in the clustering patterns as potentially important to predicting the risk of developing cancer. Cluster labels will be generated from the training data only to avoid data leakage and added as variables to both the training and test sets in all models.

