A range of ML methods will be used for the analysis. These algorithms will cluster, classify or identify variables according to their levels of importance in predicting cancer outcomes, aiding in variable selection and prediction model development. Unsupervised ML techniques can explore extensive datasets and examine data without predefined constraints. Supervised ML techniques, however, are still capable of analysing extensive datasets, but in the presence of predefined labels. Using both methods allows for the integration of diverse results from various methodologies, which may strengthen our findings and prediction performance.^16
17^

ML methods and specifically ML prediction modelling have been previously applied to predict certain outcomes for PWH. In clinical care for PWH, ML methods have been applied to predict viral suppression among PWH^18^ and predict who is most at risk of disengaging from ART care.^19^ Similar to the aim of our project, ML methods have been previously applied to develop cancer risk prediction models, but not specifically for PWH.^20
21^ Supervised ML models have been applied to predict the occurrence of cervical precancerous lesions among PWH.^17^ ML methods have also been used to predict comorbidity outcomes as defined by the Charlson Comorbidity Index, which includes cancer, but not as an isolated outcome.^22^ These methods have not yet been applied, to our knowledge, specifically to predict the risk of CRC occurrence among PWH.

In summary, there is a need for updated recommendations and an opportunity to personalise CRC screening recommendations for PWH using robust methods of analysis. This study will aim to develop high-quality risk prediction models by applying various robust ML methods in an ensemble model and comparing it to a baseline Cox PH model. The findings will support model development and provide high-performing tools to help personalise CRC screening recommendations.

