### Study aims

The aim of this study is to apply a range of ML methods to analyse comprehensive datasets collected from nationwide demographic and health registers in Sweden to develop CRC risk prediction models for PWH, additionally using data from PWoH and compare the performance to a Cox PH regression model prediction baseline. Additionally, the aim is to evaluate the importance of variables to the prediction models.

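### Variables that define clusters formed without the outcome are read as potentially important for colorectal cancer, although that ranking never uses colorectal cancer

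*Protocol article*

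**What the plan says.** In the protocol article, section ML ensemble model—unsupervised ML, the clusters are formed without the outcome: "K-means clustering will be used to group unlabelled data into the pre-estimated number of distinctive clusters depending on their distances from each other". Hierarchical clustering likewise merges the observations that are most alike. The number of clusters is "determined using both the Calinski-Harabasz Index and Silhouette Scores", and neither index uses CRC.

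The section then links the clusters to CRC importance in three places:
- It says that interpreting the most decisive clustering variables, with the help of decision trees, allows their importance for predicting the outcome to be evaluated.
- "Decision trees will be used to aid interpretation of the clustering decisions from both analyses to determine the important contributing variables to the outcome".
- "If a difference in the clustering patterns over the outcome is observed", then "we can interpret the most determining variables in the clustering patterns as potentially important to predicting the risk of developing cancer".

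The comparison behind the third statement is open-ended: "The clustering analyses will be used to observe any differences in the clustering patterns across the outcomes".

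Variable importance is a stated aim of the study (Study aims): "Additionally, the aim is to evaluate the importance of variables to the prediction models". The Introduction says that the algorithms, clustering included, will "identify variables according to their levels of importance in predicting cancer outcomes, aiding in variable selection and prediction model development".

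Separately, the section ML ensemble model—supervised ML assesses importance with models fitted to CRC: penalised Cox coefficients, survival trees, random survival forests, XGBoost, and SHAP values for each base learner.

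**The concern.** A tree that explains cluster membership shows which variables separate the clusters. It does not show which variables are related to CRC. The section treats the first as evidence of the second as soon as CRC differs between clusters.

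Such a difference can arise because one risk factor is mildly unbalanced between clusters that were formed by quite different variables. The rule would credit those other variables. A strong risk factor that does not separate the clusters would not be named.

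At stake is the importance aim. The study would produce two accounts of which variables matter for CRC. One of them ranks variables without reference to CRC, and the text does not say which account takes precedence.

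**Working it through.** **1. Structure of the rule.** Let X be the covariates and Y be CRC.
- Cluster labels: C = f(X). The data are unlabelled and the number of clusters is chosen by internal indices.
- Variable ranking: R = g(X, C) = g(X, f(X)).
- Trigger: T = h(Y, C), a single yes or no for the whole clustering.
- Conclusion: if T is yes, read the top of R as potentially important for Y.

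Y enters only through T. Replace CRC by any other outcome that also differs between the clusters, and the list of variables is identical. This holds for K-means and for hierarchical clustering, and for any definition of T, including a significance test.

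**2. Illustration.** The plan attaches no figure to this rule, so there is none to reproduce. Inputs taken from Data preparation:
- 13 000 people with HIV plus 130 000 without, 80% for training: 0.8 × 143 000 = 114 400.
- People with HIV only: 0.8 × 13 000 = 10 400.
- About one of six time blocks: 114 400 / 6 ≈ 19 000 (the number of blocks is assumed).
- CRC risk: 129.1 per 100 000, taken as yearly, × 10 years = 1.29%.

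Assumed, because the article does not give the covariate structure: eight standardised variables. Four have no effect on CRC and form two latent groups (40/60, 2 SD apart). Two are true risk factors (log HR 0.7 per SD). Two are noise. K-means was run with two clusters, and variables were ranked by the Gini gain of a single split on the cluster label. There were 60 runs at 114 400 and 200 at each smaller size.

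| True factors and the latent groups | CRC difference at p<0.05 (N = 114 400 / 19 000 / 10 400) | No-effect variable ranked first | Mean true factors in top four (of 2) | Median CRC risk ratio |
|---|---|---|---|---|
| Unrelated | 8% / 5% / 4% | 100% | 0 | 1.04–1.14 |
| One differs by 0.3 SD | 100% / 46% / 26% | 100% | 0 | 1.24–1.27 |
| One differs by 0.6 SD | 100% / 90% / 82% | 100% | 0 | 1.50–1.58 |
| Both differ by 2 SD | 100% / 100% / 100% | 63–68% | 1.2–1.4 | 7.4–7.5 |

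Some difference in CRC proportion, of any size, was seen in 100% of runs in every row. The same was true in further runs where no variable affected CRC; there a 5% test was significant in 8% (N = 114 400) and 5.5% (N = 19 000).

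**3. Reading the rows.**
- *0.3 SD row.* The expected ratio is about exp(0.7 × 0.3) = exp(0.21) = 1.23, against 1.24 simulated at the largest size. The whole difference comes from one true factor, and that factor never reached the top four.
- *2 SD row.* Six variables now separate the clusters equally, four of them without effect. A random draw among the six would put a no-effect variable first in 4/6 = 67% of runs and 4 × 2/6 = 1.33 true factors in the top four. The simulated 63–68% and 1.2–1.4 are about what chance gives. The true factors are found because they define the clusters, not because they matter for CRC.

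**4. A second assumed structure.** With nine variables, CRC was driven only by age and one comorbidity of 5% prevalence, and education and marital status were merely correlated with age. Clusters differed at p<0.05 in 100% of 100 runs. The top variable had no effect in 84%, and 78% of tree importance went to no-effect variables. Mean importance of age was 0.00, so about 22% went to the comorbidity, a true factor.

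**Limits.** Hierarchical clustering was not simulated. The number of clusters was fixed at two in the first structure and chosen by silhouette alone in the second, whereas the plan uses two indices. The rates belong to the assumed structures. Step 1 does not depend on them.

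**The case against.** The strongest reply is that this is an exploratory step, hedged in the text, beside a full set of outcome-based importance measures. Much of that stands.

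- *Hedging.* The sentence on the observed difference speaks only of potential importance. The sentence on decision trees has no such hedge: it gives finding the contributors to the outcome as the trees' purpose.
- *How often the rule applies.* A reader might infer that it would apply in nearly every dataset. That holds only if any difference counts, or if the clusters are related to risk in a large sample. With a 5% test and clusters unrelated to CRC, the simulations gave about 3–8% per look. A threshold may sit in a fuller plan, so its absence is not the point here. A threshold would settle whether CRC differs between clusters, but not which variables are responsible.
- *How often it misleads.* A reader might infer that the rule always names the wrong variables and misses the right ones. It does not: true factors are partly found when they happen to drive the clusters.
- *Damage to the models.* A reader might infer that the rule distorts variable selection. No passage lets cluster-tree rankings remove variables from the supervised models. The Introduction's sentence on variable selection covers all the algorithms together, and the baseline Cox model takes its variables from the literature. Only cluster labels pass into the models, where learners fitted to CRC can down-weight them.

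What the reply does not remove is the inference itself. It remains in the text as a second route to importance, with no stated precedence.

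**Conclusion.** The concern holds in a limited form. The step from cluster-defining variables to importance for CRC is invalid by construction, because the ranking makes no use of CRC. It can name variables with no effect and miss real risk factors.

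The frequency is unknown, because it depends on a covariate structure that the article does not give. The simulated 63–100% (first structure) and 84% (second) for a no-effect variable ranked first illustrate the mechanism; they are not forecasts for these registers. No effect here means no contribution once the true factors are in the model. Such a variable may still be a proxy for CRC through cluster membership.

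The consequence is confined to the cluster-based importance statements and their interpretation. The documents do not support a claim that the prediction models are compromised or that real risk factors would go undetected in the study as a whole. The text should be changed because importance is a stated aim and the remedy is cheap.

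**What to change.** In ML ensemble model—unsupervised ML:
- Delete the inference in "we can interpret the most determining variables in the clustering patterns as potentially important to predicting the risk of developing cancer", the parallel statement that importance for the outcome can be evaluated from the decisive clustering variables, and the closing purpose clause of "Decision trees will be used to aid interpretation of the clustering decisions from both analyses to determine the important contributing variables to the outcome".
- Say instead that the trees describe which variables characterise the clusters, and that CRC frequency by cluster is reported descriptively.

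State that variable importance, and any variable selection, rests on the measures already planned in ML ensemble model—supervised ML: SHAP values, penalised coefficients, and survival forest and XGBoost importance.

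Judge the cluster labels by fitting the same model with and without them and comparing the held-out concordance index or Brier score, both already listed in Stacking and dissemination.

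The cost is a wording change and one extra model comparison. No data and no planned outcome-based analysis are lost, and the cluster trees stay as description.

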#### ML ensemble model—supervised ML

Elastic Net regularisation, XGBoost, Random Survival Forests and decision trees will be used to develop the ensemble model for predicting CRC risk. For Elastic Net regularisation, a Cox PH model with an Elastic Net penalty will be used to estimate relative risk and interpret variable importance via the penalised regression coefficients. The resulting model additionally highlights influential predictors by minimising less important coefficients towards zero, indicating lower contribution to predicting the outcome.^40^

Decision trees are tree-based models that split data based on variable thresholds to make predictions. Decision trees suited for survival time-to-event data will be used. This method will estimate the probability of cancer over time. This model may additionally be used to infer how much each variable contributes to reducing dataset impurity at each split,^41^ contributing to our understanding of which variables are most valuable to the outcome prediction. Random Survival Forest models work similarly to decision trees but aggregate results across many trees, providing more robust estimates of variable importance and potentially improved performance for risk prediction. XGBoost uses built-in optimisation techniques to develop high-performing prediction models.^42^ The output of the XGBoost model may additionally be used to assess the predictive value of individual variables.

Out-of-fold predictions from each model will be stored to serve as inputs for the meta-learner. Additionally, SHapley Additive exPlanations (SHAP) values will be computed for each trained base learner to assess variable contributions and enhance model transparency.

#### Stacking and dissemination

Stacking, an ensemble learning method, will be used to combine predictions from the previously described ML models.^43^ The base learners will generate out-of-fold risk scores using Time Series Split, which will then serve as inputs to a Cox-PH model as the meta-learner. Finally, the trained base learners and meta-learner will then be used to generate final risk score predictions on the test set.

The performance of the stacked models will be primarily evaluated using balanced accuracy,^44^ and additionally assessed with the concordance index,^45^ Brier score,^46^ time-dependent area under the curve and area under the precision-recall curve (AUPRC), before variable importance is assessed.^13
47
48^ All metrics will be thoroughly considered, but the balanced accuracy of each prediction performance will be weighted most due to its handling of class imbalance, considering both sensitivity and specificity.^44^ AUPRC is preferred over area under the receiver operating curve due to its ability to better handle class imbalance, which will be a factor in this study.^49^

The model reporting will adhere to the TRIPOD+AI statement.^50^ The variable importance results will additionally be considered separately. A summary of the analysis plan is illustrated in figure 2.

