### Study population

The study population will include all resident PWH and PWoH, 18 years or older, born between 1940 and 2008, who resided in Sweden at any time point between 1983 and 2024. The study period will span from 1 January 1983 to 31 December 2024. The inclusion date will be the day the person turns 18, the start date of residency in Sweden, or the study start date, whichever occurs last. Follow-up will continue until emigration, death, end of study time or until 6 months before the first incident of CRC. The outcome of interest is CRC. See figure 1 for an illustration of the inclusion criteria and how inclusion and the follow-up period were defined.

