#### Data preparation

For this study, we will use complete cases only since missing data are minimal. Variables missing more than 10% of the data will be omitted, and after that, any observations with missing data will be dropped.^32^ For the ML analyses, the data will be split 80% into training and 20% into test sets based on follow-up time. The variables in each set will be further prepared to optimise their analysis. Categorical variables will be transformed using one-hot encoding. Normalisation and standardisation of variables will be applied where necessary.

The participants will be matched 1:10 using the entire HIV-negative population in Sweden that fit the criteria. They will be matched on age, legal sex, region of birth and comorbidities including hypertension, chronic obstructive pulmonary disease, diabetes and previous cancer diagnosis.^33
34^ The standardised mean difference of the cohorts will be compared from before and after matching to confirm consistency. Power was calculated using the full anticipated study population consisting of just over 13 000 PWH matched 1:10 to approximately 130 000 PWoH. Median follow-up time is estimated to be at least 10 years in both groups. The expected incidence rate of CRC used for the calculation was the Swedish age-standardised incidence rate reported by the European Commission (129.1 per 100 000 population).^35^ Based on these assumptions and using a two-sided alpha of 0.05, the study is estimated to have 80% power to detect an HR of approximately 1.20 or greater.

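### Time Series Split leaves the first 1/(k+1) of the training set without an out-of-fold score, so the Cox meta-learner is fitted on a selected subset with scores of unequal quality

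*Protocol article*

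**What the plan says.** Under *ML ensemble model—unsupervised ML* the protocol article says that "Time Series Split cross-validation (CV) will be used during model training and meta-learning stages". Under *ML ensemble model—supervised ML* it names the base learners: "Elastic Net regularisation, XGBoost, Random Survival Forests and decision trees will be used to develop the ensemble model for predicting CRC risk". Under *Stacking and dissemination* it says how they are combined: "The base learners will generate out-of-fold risk scores using Time Series Split, which will then serve as inputs to a Cox-PH model as the meta-learner". No other input to the meta-learner is named, and nothing is said about people who receive no out-of-fold score.

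Two time variables appear elsewhere. Under *Data preparation*, "the data will be split 80% into training and 20% into test sets based on follow-up time". Under *Study population*, "The inclusion date will be the day the person turns 18, the start date of residency in Sweden, or the study start date", taking the latest of the three. Neither is named as the order for the cross-validation, although follow-up time is the only one tied to any split.

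**The concern.** Time Series Split is built for a single series in which later observations depend on earlier ones. Here the units are separate people, and the scheme has two side effects when its output feeds a stacking model.

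- **Unscored block.** The first block is never held out. Whatever the ordering variable, its members have no score and cannot enter a Cox model whose covariates are scores. They are missing by position in the ordering, not at random.
- **Unequal scores.** Early scores come from learners trained on a small part of the data and late scores from learners trained on most of it. One set of meta-learner coefficients is fitted across all of them.

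At stake are the weights that decide how much each machine-learning method contributes, and so the ensemble that is compared with the baseline Cox model, a stated study aim.

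**Working it through.** The plan gives no figure for folds, first-block size or events lost, so there is none to reproduce.

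**Inputs from *Data preparation*:** about 13,000 people with HIV and 130,000 matched controls (143,000); an 80% training share; 129.1 cases per 100,000 a year; median follow-up of at least 10 years, used here as a 10-year mean. **Assumed:** one row per person; k = 3, 5 or 10.

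**Step 1: people without a score.** Training set: 0.8 × 143,000 = 114,400. First block = n − k × floor(n/(k+1)).

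| k | first block | share | training share of scoring learners |
|---|---|---|---|
| 3 | 28,600 | 25% | 25% to 75% |
| 5 | 19,070 | 16.7% | 16.7% to 83.3% |
| 10 | 10,400 | 9.1% | 9.1% to 90.9% |

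The scoring learners use i/(k+1) of the data for i = 1 to k, which averages 1/2. Ordinary K-fold leaves nobody unscored and trains every scoring learner on 80% (5 folds) or 90% (10 folds).

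**Step 2: events lost to the meta-learner.** The documents give no age-specific rates and no distribution of inclusion dates, so this needs simulated cohorts that follow the *Study population* entry rule. Assumptions varied: birth-year distribution, migrant share (0–70%), cancer hazard constant or proportional to age to the power 4 or 5, and extra pre-1997 mortality of 0–5% a year.

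- *Inclusion-date order:* 33–52% at k = 3, 19–35% at k = 5 and 11–20% at k = 10 in one set of cohorts. With birth years uniform from 1940 to 2006 and hazard rising as age to the power 5, the k = 3 share reaches about 59%. Overall: roughly 11–59%.
- *Follow-up-time order, k = 5:* from near 0% to about half. One set gave 0.3–9% shortest-first and 24–52% longest-first; another gave 2–22% shortest-first. The direction-specific figures are fragile. Cancer itself ends follow-up, so people followed to the study end are event-free by definition, and the share in each end block depends heavily on assumed attrition.

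**Step 3: precision.** Expected events: 143,000 × 10 × 129.1/100,000 = 1,846. If the split is neutral with respect to events, 0.8 × 1,846 = 1,477 fall in training. Losing 11% leaves 1,477 × 0.89 = 1,315; losing 59% leaves 1,477 × 0.41 = 606. Four base learners mean four coefficients, so even the worst case leaves about 606/4 = 151 events per coefficient.

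**Step 4: effect on discrimination.** Eight small survival simulations (about 140 events, k = 5, the four named learners, random hold-out) compared Time Series Split with stratified 5-fold. The mean C-index was lower with Time Series Split by about:

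- 0.004 in inclusion-date order (about 38% of events lost);
- 0.011 with longest follow-up first;
- 0.19 with shortest follow-up first.

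Follow-up time is part of the outcome, so blocks ordered on it differ systematically in event times. That makes a large loss plausible there.

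**The case against.** The strongest reply is that fold number, ordering, row structure and handling of the first block are details an article leaves to the full plan or code, and that time-ordered validation is a recognised design in keeping with a time-based train/test split. The first part stands for k and the ordering: their absence is not the finding. But Time Series Split as the source of the meta-learner's inputs is a stated choice, and the unscored first block follows for every k and every ordering of one-row-per-person data. With person-period rows the lost block would be early person-time rather than whole people; the article does not describe such rows.

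It also stands that first-block members still train the base learners, and that precision is not a practical problem (Step 3).

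A reader might infer more than the documents support:

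- *About a third of events are lost.* This needs k = 5, inclusion-date order and a steep age curve. None is given.
- *The lost block is the oldest, longest-followed people.* Everyone adult and resident on 1 January 1983 shares one inclusion date. In the simulations 14–43% of a randomly split training set did. Where that exceeds the block, membership depends on arbitrary tie order.
- *The weights tilt towards the penalised Cox learner and against the ensemble.* A small binary stand-in gave boosting a weight of 0.12–0.13 with Time Series Split against 0.22–0.23 with 5-fold. The run-to-run SD was about 0.2 over 10 runs, and AUC differed by no more than 0.002. That is not evidence of a direction.
- *The problem is worst among people with HIV only.* *Substudy—PWH only* plans a simple Cox model and exploratory machine learning. It does not commit to stacking.

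**Conclusion.** The point holds as a flaw in a stated method. With one row per person, between 9.1% (k = 10) and 25% (k = 3) of the training set is unscored and lost to the meta-learner, and the remaining scores are of very unequal quality. The event share lost cannot be fixed from the documents; the ranges in Step 2 rest on assumed age curves, birth years, migration and attrition.

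The consequence is selection and mis-tuned weights. In the one check run on survival data it was minor in inclusion-date order and serious with shortest follow-up first, while Time Series Split was on average no better than stratified 5-fold under any ordering tried. Those simulations are few and small, so the differences show the pattern rather than the size to expect in the registers.

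**What to change.** In *ML ensemble model—unsupervised ML* and *Stacking and dissemination*, generate the out-of-fold scores by 5- or 10-fold cross-validation within the training set, stratified on colorectal cancer and HIV status. Keep each person with HIV and their matched controls in the same fold, and do the clustering inside each training fold. Every training-set member then has exactly one score. If performance over calendar time is of interest, add a separate temporal check ordered by calendar date and keep it out of the stacking step.

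If Time Series Split is retained, state the ordering variable, the tie rule, the number of splits and how the first block enters the meta-learner, and do not order by follow-up time.

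Cost: a change of wording and of one cross-validation object in the code, with no new data. Computing time rises somewhat, and the inner folds no longer mimic forward-in-time prediction; the temporal check covers that.

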#### Cox PH regression

A Cox PH regression model will be used as a baseline performance comparison for the ML methods. This model will favour the simplest approach, and the use of prior knowledge supported by literature will select the most relevant variables. The model performance will then be considered to develop the model for the prediction of cancer among PWH.

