### Clinical relevance

The CRC risk prediction model for PWH will be developed with the aim of supporting risk-stratified CRC surveillance within routine HIV care. The Swedish national CRC screening programme currently invites the general population aged 60–74 years for biennial faecal testing^51^ and does not account for HIV-specific risk factors. A validated risk prediction model could be integrated into the InfCareHIV decision-support interface used at all Swedish HIV clinics, enabling treating physicians at routine annual follow-up to identify individuals who may benefit from earlier screening initiation, shorter screening intervals or referral for colonoscopy. Before clinical deployment, the model will require external validation in independent cohorts and prospective evaluation of its effect on screening uptake, diagnostic yield and stage at diagnosis.

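### Model performance is judged on all adults pooled, with a literature-variable Cox model as the only benchmark, so the planned comparison cannot show whether either model adds anything to age

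*Protocol article*

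**What the plan says.** Under Study population, the cohort is defined broadly: "The study population will include all resident PWH and PWoH, 18 years or older, born between 1940 and 2008". Follow-up ends on 31 December 2024, so attained ages run from 18 to about 84.

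Under Data preparation, "the data will be split 80% into training and 20% into test sets based on follow-up time", and the HIV-negative comparators are matched 1:10: "They will be matched on age, legal sex, region of birth and comorbidities".

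The benchmark is set under Cox PH regression: "A Cox PH regression model will be used as a baseline performance comparison for the ML methods". Its variables are to come from prior knowledge, and the article does not list them.

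Under Stacking and dissemination, "Finally, the trained base learners and meta-learner will then be used to generate final risk score predictions on the test set". The same section ranks the metrics: "The performance of the stacked models will be primarily evaluated using balanced accuracy", followed by concordance, Brier score, time-dependent AUC and AUPRC. None is described as age-stratified or age-adjusted. The Substudy in people with HIV applies the same methods.

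The intended use is under Clinical relevance. The section first describes current practice: "The Swedish national CRC screening programme currently invites the general population aged 60–74 years for biennial faecal testing". The model is then meant to "identify individuals who may benefit from earlier screening initiation, shorter screening intervals or referral for colonoscopy".

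**The concern.** Present screening already selects people by age. A model that personalises screening has to tell clinicians something that date of birth does not. In a test set spanning all adult ages, most case/non-case pairs differ widely in age, and any model containing age will order those pairs well whatever else it contains.

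The planned Cox comparator does not isolate this. If both competitors include age, both get the same credit for it, and the difference between them says nothing about the value of either beyond age. The study could report respectable discrimination and a clear winner between stacking and Cox while the question behind its stated purpose stays unanswered. The Dissemination plan sends the findings to guideline bodies, so readers are likely to take the headline figure as evidence of personalisation.

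**Working it through.** The article gives no expected performance figure, so there is none to reproduce. Its one computed result, the power statement, concerns the hazard ratio for HIV and does not bear on this point. The check asks what age alone would score.

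**Inputs from the article**
- Ages from 18; births from 1940, so 2024 − 1940 = 84 at most (Study population).
- Incidence 129.1 per 100 000, read as per person-year; median follow-up at least 10 years, taken as a mean of 10; 13 000 people with HIV and 130 000 without; 20% test set (Data preparation).

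**Assumptions not in the article**
- Hazard proportional to age^k, with k = 3 to 6.
- Three illustrative age distributions: uniform 18-74; normal with mean 45, SD 13; normal with mean 38, SD 11. The normal distributions are cut at 18 and 84.

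**Formulas**
- Ten-year risk at age a is proportional to (a+10)^(k+1) − a^(k+1), scaled to a mean of 10 × 129.1/100 000 = 1.29%.
- Concordance of age alone = P(case older than non-case), cases weighted by risk and non-cases by 1 − risk.
- Balanced accuracy = (sensitivity + specificity)/2 at the best single age cut-off.

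An example with k = 5 shows the mechanism. Age 65 against 25: (75^6 − 65^6)/(35^6 − 25^6) = 1.0256×10^11 / 1.594×10^9 ≈ 64. Age 59 against 50: (69^6 − 59^6)/(60^6 − 50^6) = 6.574×10^10 / 3.103×10^10 ≈ 2.1.

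**Age alone: concordance (balanced accuracy)**

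| Ages | k=3 | k=4 | k=5 | k=6 |
|---|---|---|---|---|
| Uniform 18-74 | 0.73 (0.67) | 0.77 (0.71) | 0.80 (0.74) | 0.83 (0.76) |
| Normal 45, SD 13 | 0.69 (0.64) | 0.74 (0.67) | 0.78 (0.71) | 0.81 (0.74) |
| Normal 38, SD 11 | 0.68 (0.63) | 0.73 (0.67) | 0.77 (0.70) | 0.81 (0.73) |
| 40-59 only | 0.59 (0.57) | 0.62 (0.59) | 0.64 (0.61) | 0.67 (0.63) |
| 50-59 only | 0.54 (0.53) | 0.56 (0.54) | 0.57 (0.55) | 0.58 (0.56) |

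Extending the uniform case to 84 raises its figures by about 0.01.

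**Using the article's entry rule.** Entry is at the latest of the 18th birthday, start of residency or 1983, so lifelong residents enter at 18 to 43 (1983 − 1940 = 43). In a simulation of this rule, Harrell's C for entry age alone was 0.64-0.73 with no immigrants and 0.72-0.83 with an assumed immigrant share of one half (k = 3 to 6).

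**How far real non-age information moves the pooled figure.** Simulations added one standard-normal non-age score with a hazard ratio of 1.3 to 1.5 per SD. Pooled AUC rose by about 0.005-0.03 and balanced accuracy by about 0.003-0.024. Within ages 50-59, AUC rose from 0.54-0.58 to 0.58-0.64. For example, with a mean age of 42 (SD 12), k = 4 and a hazard ratio of 1.5, pooled AUC went from 0.736 to 0.757. Age then accounts for (0.736 − 0.5)/(0.757 − 0.5) = 92% of the excess over 0.5. Within 50-59 the same score moved AUC from 0.559 to 0.631.

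**Events available.** Pooled: 143 000 × 10 × 129.1/100 000 = 1846, of which 20% is about 369. People with HIV: 13 000 × 10 × 129.1/100 000 = 168, of which 20% is about 34. This assumes that events divide in proportion to the split.

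**The case against.** The stated statistical aim is ensemble against Cox, and age does not bias that contrast. This stands: the comparison is valid for its own question. But the article also claims a purpose, personalised screening, which that contrast does not test.

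Several planned features might seem to supply the missing comparison.
- Matching on age balances people with and without HIV. It does not balance cancer cases and non-cases.
- SHAP values and variable importance would reveal that age dominates, but do not measure performance gained over it.
- The Introduction promises subgroup analyses without naming age, so an analysis plan not shown may contain some. The article itself, however, fixes the comparator and the metrics.
- The Cox model is to be kept simple and could turn out close to age and sex. Its variables are not listed and the supplementary table is not shown, so this cannot be relied on. For the same reason, the inclusion of age as a predictor is likely but unconfirmed.

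A reader might also infer four stronger things that the documents do not support.
- **That the evidence must come from people under 60.** Clinical relevance lists shorter intervals and referral as well as earlier start, and those two uses are not confined to people under 60. Under the entry rule few people enter at 40 or over, so an evaluation at ages 40-59 would need later prediction times that the article does not describe.
- **That screening distorts performance at 60-74.** The article gives no start date, uptake or effect of the programme.
- **That the study could lead straight to clinical use.** Clinical relevance requires external validation and prospective evaluation first. This softens the consequence but does not supply the benchmark.
- **That pooled performance is bound to be mostly age.** That rests on an assumed gradient.

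**Conclusion.** The point holds in a limited form. As written, the evaluation can rank stacking against Cox but cannot show whether either adds to age. Under the assumed gradients, age alone reaches a concordance of about 0.68-0.83 and a balanced accuracy, the article's leading metric, of about 0.63-0.76 over all ages. Its concordance within ages 50-59 is about 0.54-0.58. With the article's entry rule simulated, the all-ages concordance for entry age alone is 0.64-0.83.

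The exponents, age distributions and immigrant share are assumptions, and the exact values should not be read as forecasts. The direction was the same in every case tried. A good pooled figure is compatible with no personalisation, and a modest gain over age can be real yet barely visible in it. This limits what may be concluded; it does not invalidate the planned ML-versus-Cox comparison.

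**What to change.** Under Cox PH regression and Stacking and dissemination:

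1. Add a Cox model with age and sex only as a reference, fitted and tested on the same data as the other models.
2. Report the gain of the literature-variable Cox model and of the stacked model over this reference in balanced accuracy, concordance, time-dependent AUC, Brier score and AUPRC, with intervals, for the pooled test set and for the substudy in people with HIV.
3. Add age-adjusted concordance (pairs compared within age bands) as a secondary result.
4. State that any claim of personalisation rests on the gain over age and sex, not on the pooled figure.

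The cost is one simple model and some extra tabulation, with no new data. The headline will look less favourable. Estimates among people with HIV will be imprecise, with about 34 test-set events against about 369 pooled, and the report should say so.
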